**Fig 1 pone.0357593.g001:**
[figure not shown]
SPIRIT schedule of enrollment, interventions, and assessments. The screening period (−t_1_) is completed within 7 days before randomization. Mid-intervention assessment (t_1_) is performed at week 4, post-intervention assessment (t_2_) at week 8, and follow-up assessment (t_3_) at week 12. Participants in the two intervention groups attend two treatment sessions per week (16 sessions over 8 weeks). For the intervention groups, the week-4 assessment corresponds to the eighth treatment session, whereas for the waitlist control group it corresponds to the second study visit. Arrows indicate the continuous 16-session intervention period for the two intervention groups. Abbreviations: SCID-5, Structured Clinical Interview for DSM-5; PC-PTSD-5, Primary Care PTSD Screen for DSM-5; ECG, electrocardiogram; ETE, Emotion-to-Emotion Therapy; VR, virtual reality; PCL-5-K, Korean version of the PTSD Checklist for DSM-5; CGI-I, Clinical Global Impression–Improvement scale; K-PTGI, Korean version of the Posttraumatic Growth Inventory; FFMQ-S, Five Facet Mindfulness Questionnaire–Short Form; PHQ-15, Patient Health Questionnaire-15; HADS, Hospital Anxiety and Depression Scale; ISI-K, Korean version of the Insomnia Severity Index; EQ-5D-5L, EuroQol 5-Dimension 5-Level; EQ-VAS, EuroQol visual analogue scale; MRM, Mentalizing the Rooms of Mind; CSEI-S, Core Seven-Emotions Inventory–Short Form; SUDS, Subjective Units of Distress Scale; HRV, heart rate variability; QEEG, quantitative electroencephalography.

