### Interventions

The interventions are reported in accordance with the Template for Intervention Description and Replication (TIDieR) checklist [11] (S6 File). The intervention consists of three sequential phases: (1) a screening phase, (2) an 8-week treatment phase, and (3) a follow-up assessment at week 12. Participants allocated to the VR-ETE and standard ETE groups receive 16 treatment sessions over 8 weeks (two sessions per week, 40 minutes per session). Both active interventions are delivered individually, one clinician to one participant, face-to-face in an outpatient consultation room at each study site; no group sessions and no remote or unsupervised home sessions are used. Participants allocated to the waitlist control group continue their usual daily activities for 8 weeks while receiving fortnightly telephone monitoring. They attend the same assessment visits as the intervention groups at baseline, week 4, week 8, and week 12 but do not receive the study intervention during the randomized phase.

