### Outcome measures

The primary outcome measure is the Korean version of the PTSD Checklist for DSM-5 (PCL-5-K), a 20-item self-report measure of PTSD symptom severity with a total score ranging from 0 to 80. The PCL-5-K is administered at baseline, week 8, and week 12, with week 8 designated as the primary endpoint [14].

Secondary outcome measures include the Clinical Global Impression–Severity Scale (CGI-S) and Clinical Global Impression–Improvement Scale (CGI-I) [15], the Korean version of the Posttraumatic Growth Inventory (K-PTGI) [16], the Five Facet Mindfulness Questionnaire–Short Form (FFMQ-S) [17], the Patient Health Questionnaire-15 (PHQ-15) [18], the Hospital Anxiety and Depression Scale (HADS) [19], the Korean version of the Insomnia Severity Index (ISI-K) [20], and the Hwa-Byung Scale [21]. Hwa-Byung (火病, literally “fire illness”) is a Korean culture-bound syndrome characterized by suppressed anger with combined psychological and somatic manifestations; the Hwa-Byung Scale is a 31-item self-report instrument comprising a 15-item symptom subscale and a 16-item personality subscale, each item rated on a 5-point scale (0–4), with higher scores indicating greater severity [21]. Secondary outcome measures are administered at baseline, week 8, and week 12, as applicable. The CGI-S is administered at baseline to characterize overall illness severity. The CGI-I is administered only at weeks 8 and 12 to evaluate improvement relative to the pretreatment condition; no CGI-I score is assigned at baseline.

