The CSEI-S and the SUDS are administered immediately before and after each intervention session. The CSEI-S is used to assess changes in core emotional states [22]. The SUDS, originally introduced by Wolpe and Lazarus, is a brief self-report rating of momentary subjective distress and is used to support session-level clinical monitoring [23]. Because it is used here for within-session clinical monitoring rather than as a validated confirmatory endpoint, the SUDS will be treated as an exploratory session-level measure. MRM is administered at the same time points as a projective drawing-based clinical technique. Participants visualize and depict their current internal experiences as rooms representing thoughts, emotions, memories, distress, and psychological resources. MRM is used to support clinical assessment, self-reflection, treatment-module selection, and qualitative monitoring of psychological change [12]. It is not treated as a standardized continuous efficacy outcome.

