### Economic evaluation

The economic evaluation is designed as a 12-week within-trial analysis. The EuroQol 5-Dimension 5-Level instrument (EQ-5D-5L) and the EuroQol visual analogue scale (EQ-VAS) are administered at baseline and at weeks 4, 8, and 12 [24]. EQ-5D-5L utility scores will be derived using the Korean EQ-5D-5L value set and used to calculate quality-adjusted life-years (QALYs) using the area-under-the-curve method, with linear interpolation between assessment points. Cost data are collected at the same assessment time points using a purpose-built cost questionnaire covering direct medical costs, direct non-medical costs, and indirect costs attributable to productivity loss. In-trial intervention costs are calculated by multiplying the recorded number of sessions by the corresponding prespecified unit costs. After unblinding, researchers obtain costs incurred at the study sites from the participating sites’ billing and electronic records. All resource-use costs will be valued in 2026 Korean won. Where cost inputs originate from earlier calendar years, they will be converted to the 2026 price year using the Korean Consumer Price Index. Because the analytic time horizon is 12 weeks and therefore less than 1 year, neither costs nor health outcomes will be discounted. The economic evaluation will follow the relevant recommendations of the Korean pharmacoeconomic evaluation guideline [25] and the CHEERS 2022 reporting standards [26]. Productivity loss is valued using the human-capital approach because the cost questionnaire does not collect the return-to-work timing data required to apply the friction-cost method.

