#### Secondary and exploratory analyses.

Continuous secondary outcomes measured at week 8—the K-PTGI, FFMQ-S, PHQ-15, HADS, ISI-K, and Hwa-Byung Scale total scores—will each be analyzed using a separate ANCOVA, with the week-8 score as the dependent variable and the corresponding baseline score, treatment group, and study site included in the model. These analyses will be considered secondary or exploratory, and adjusted mean differences with 95% confidence intervals will be reported. QEEG parameters (absolute power, relative power, z-scores, and interelectrode coherence across the delta, theta, alpha, beta, and gamma frequency bands) and HRV parameters (SDNN, RMSSD, LF, HF, and LF/HF) measured at week 8 will be analyzed using the same ANCOVA framework, with the corresponding baseline value and study site included as covariates. Each physiological parameter will be modeled separately rather than entering multiple highly correlated QEEG or HRV indices simultaneously as predictors. To control the false discovery rate across the complete physiological outcome family, the Benjamini–Hochberg procedure will be applied jointly to the full set of prespecified QEEG and HRV hypothesis tests, including all electrodes, frequency bands, coherence pairs, and HRV indices. Both unadjusted and adjusted p values will be reported, and statistical interpretation will be based primarily on the adjusted values, effect sizes, and 95% confidence intervals. These high-dimensional physiological analyses will be considered exploratory.

The persistence of treatment effects through week 12 will be examined using a mixed-effects model for repeated measures including the post-baseline observations at weeks 8 and 12. The model will include treatment group, assessment time, the treatment-group-by-time interaction, the corresponding baseline outcome score, and study site. Within-participant correlations will be accounted for using an appropriate repeated-measures covariance structure. Adjusted between-group differences at weeks 8 and 12 will be reported. This model will be applied to the primary outcome (PCL-5-K) and, as exploratory analyses, to the K-PTGI, FFMQ-S, PHQ-15, HADS, ISI-K, and Hwa-Byung Scale total scores.

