#### Missing data.

Missing week-8 efficacy data will be addressed using multiple imputation under a missing-at-random assumption. The imputation model will include randomized treatment group, baseline and available post-baseline outcome measurements, and study site. The primary ANCOVA will be fitted to each imputed dataset, and estimates will be combined using Rubin’s rules. Sensitivity analyses will include a mixed-effects model using all available longitudinal observations and, where appropriate, complete-case analysis. The PP analysis will provide an additional supportive sensitivity analysis. Except for multiplicity-adjusted comparisons, statistical tests will be two-sided with a significance level of 0.05.

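### No PTSD symptom scale is taken in all arms between baseline and week 8, so for participants lost before week 8 the planned missing-data analyses are not independent checks

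*Protocol article*

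**What the plan says.** The primary scale has three time points: "The PCL-5-K is administered at baseline, week 8, and week 12, with week 8 designated as the primary endpoint" (Outcome measures). The other clinical scales follow the same schedule: "Secondary outcome measures are administered at baseline, week 8, and week 12, as applicable".

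A mid-intervention visit nevertheless exists. The Fig 1 legend says that this assessment "is performed at week 4, post-intervention assessment" following at week 8. The Interventions section says of the waitlist arm: "They attend the same assessment visits as the intervention groups at baseline, week 4, week 8, and week 12". The Economic evaluation section says that the EQ-5D-5L and EQ-VAS "are administered at baseline and at weeks 4, 8, and 12", with cost data at the same times.

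The only other measures before week 8 are tied to treatment: "The CSEI-S and the SUDS are administered immediately before and after each intervention session". The waitlist arm has no sessions.

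On missing week-8 data, the plan is multiple imputation under missing at random: "The imputation model will include randomized treatment group, baseline and available post-baseline outcome measurements, and study site". The listed sensitivity analyses are a mixed model on all available longitudinal data, a complete-case analysis where appropriate, and a per-protocol analysis. The only repeated-measures model that the article describes is one "including the post-baseline observations at weeks 8 and 12", with baseline as a covariate. The Fig 1 grid is not reproduced in the text available, so the week-4 content is taken from the prose.

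**The concern.** Multiple imputation improves on a complete-case analysis only when the imputation model holds information that the analysis model lacks. The usual source is an intermediate score on the primary scale, and this schedule does not collect one, although every arm is seen at week 4.

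The people affected are those who leave before week 8 and do not return. If some leave because they are doing badly at week 4, a model that sees only their baseline score imputes them as average members of their arm. If this happens more in the therapy arms than in the waitlist arm, the treatment effect is overstated. The sensitivity analyses would not show it, because for these people they rest on the same information and the same assumption. Agreement between them could be mistaken for robustness.

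**Working it through.** **1. The plan's own sample size.** Inputs from the Sample size section: f = 0.5, power 95%, alpha 0.05, three groups, one covariate. Using the noncentral F with df1 = 2, df2 = N − 3 − 1 and λ = f²N, the smallest N is 65 (power 0.9502), as stated. N = 72 gives 0.968. The margin covers a loss of 1 − 65/72 = 9.7%. No dropout rate is stated.

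**2. What each analysis knows about a participant lost for good before week 8.**

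| Analysis | Information on that person |
|---|---|
| Complete-case ANCOVA | none; excluded |
| Multiple imputation from PCL-5-K data | group, baseline PCL-5-K, site |
| Weeks-8/12 mixed model | no outcome row |

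Group, baseline and site are exactly the terms of the primary ANCOVA. Imputing from those terms and refitting the same model returns essentially the complete-case estimate. Treating baseline as an outcome row in the mixed model would still leave only the baseline score.

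**3. Precision.** Let d be the loss before week 8 and p the share of week-8 variance, given baseline, that a week-4 score explains. The relative variance of an arm mean is 1/(1 − d) without the week-4 score and (1 − p)/(1 − d) + p with it. Assume p between 0.11 and 0.52, and take the best case, in which all loss falls between weeks 4 and 8. At d = 0.20:
- Without week 4: 72 × 0.80 = 57.6 effective participants, power 0.920.
- With week 4, p = 0.111: 72 / (0.889/0.80 + 0.111) = 58.9, power 0.927.
- With week 4, p = 0.521: 72 / (0.479/0.80 + 0.521) = 64.3, power 0.948.

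At d = 0.10, effective N rises from 64.8 to 65.5–68.4 (power 0.949 to 0.952–0.960). At d = 0.30 it rises from 50.4 to 52.1–59.7 (power 0.877 to 0.889–0.930).

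**4. Bias.** Every input here is an assumption: SD 15; true effect 10 points; correlations 0.6 (baseline–week 4), 0.75 (week 4–week 8) and 0.5 (baseline–week 8); loss of 20% in an active arm and 5% in the waitlist arm; odds of loss rising 1.5, 2.5 or 4 times per SD of worse week-4 score. Regression imputation within arm, on several hundred thousand simulated participants, gives these effects in points:

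| Imputation uses | Mechanism in active arm only | Mechanism in both arms (20% / 5%) |
|---|---|---|
| Baseline only | about 10.5, 11.1, 11.5 | about 10.4, 10.9, 11.1 |
| Baseline + week-4 PCL-5-K | within 0.1 of 10 | within 0.1 of 10 |

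The excess of 0.4 to 1.5 points is 4–15% of 10. With the same mechanism and the same dropout rate in both arms, the baseline-only estimate returns to about 10. Adding only week-4 EQ data, with an assumed correlation of 0.5–0.7 with the concurrent PCL-5-K, removes roughly 15–40% of the bias.

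**5. Bias against sampling error.** On the same inputs with 24 per arm, the residual SD is 15 × √(1 − 0.5²) = 13.0. The standard error of a pairwise difference is 13.0 × √(1/19.2 + 1/22.8) = 4.0 points. The bias is therefore 0.4/4.0 = 0.10 to 1.5/4.0 = 0.37 standard errors. In the worst case, coverage of a 95% interval falls to about 93%.

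**The case against.** The strongest reply is that nothing here is misstated. Measuring the primary scale before treatment, after it and at follow-up is a coherent schedule, and the trial calls itself exploratory and acknowledges attrition. That stands, and it is why the point is minor.

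A reader might infer that the imputation has almost nothing to work with. The documents do not support this. Week-4 EQ data exist in all arms, and CSEI-S and SUDS scores exist in the active arms up to the last session attended. The Missing data section does not restrict the outcome measurements to the PCL-5-K, and choosing auxiliaries is often left to an analysis plan. What remains is that the text does not name these measures, that only the EQ instruments cover the waitlist arm, and that neither is a PTSD symptom scale.

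A reader might also equate stopping therapy with being lost. The withdrawal section encourages those who stop, but have not withdrawn consent for follow-up, to complete all assessments. Anyone who misses week 8 but returns at week 12 has a post-baseline PCL-5-K. The problem is confined to permanent loss before week 8, and a week-4 score would help only those lost after week 4.

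Finally, the 4–15% could be read as a prediction, which it is not. Dropout was made to depend on the week-4 score, so adding that score removes the bias by construction. The EQ-only figure also leaves out CSEI-S and SUDS. The calculation shows what could happen under a plausible mechanism, and the bias is small beside a standard error of 4.0 points.

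**Conclusion.** The point holds in limited form. No PTSD symptom scale is scheduled in all arms between baseline and the primary endpoint. For participants permanently lost before week 8, imputation from group, baseline PCL-5-K and site is essentially complete-case ANCOVA, and the weeks-8/12 mixed model adds nothing about them. The missing-data sensitivity analyses are therefore not independent checks for these dropouts.

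The possible overstatement is about 4–15% under the stated assumptions and near zero if dropout is low or equal across arms. The precision loss is modest at 10% dropout and grows with the dropout rate. The article gives no SD, correlation, dropout rate or mechanism, so the size cannot be fixed from it. The primary model, endpoint and required N of 65 are unaffected. This is a worthwhile improvement that the trial can do without.

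**What to change.** **Main change, for all participants.** In the Missing data section, name week-4 EQ-5D-5L and EQ-VAS as auxiliary variables in the imputation model for week-8 PCL-5-K. The data are already scheduled in every arm, so this costs only wording. Under the assumptions above it removes roughly 15–40% of the bias.

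**Cheap addition, for participants who have not yet reached week 4.** Give the PCL-5-K at the existing week-4 visit. Use it in the imputation model and as an extra post-baseline time point in the sensitivity mixed model. The cost is a short amendment and a few minutes of self-report.

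**Limits to state with it.** The new score will be missing for all earlier participants. That includes the entire Sanbon site, where early termination of recruitment was approved in August 2024, so its absence is tied to site as well as to calendar time. It supports the analysis only for later enrollees, whose number is not stated (recruitment is expected to finish by September 2026). It cannot help anyone lost before week 4. Later participants would also complete the primary scale once more than earlier ones.

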### Economic evaluation

The economic evaluation is designed as a 12-week within-trial analysis. The EuroQol 5-Dimension 5-Level instrument (EQ-5D-5L) and the EuroQol visual analogue scale (EQ-VAS) are administered at baseline and at weeks 4, 8, and 12 [24]. EQ-5D-5L utility scores will be derived using the Korean EQ-5D-5L value set and used to calculate quality-adjusted life-years (QALYs) using the area-under-the-curve method, with linear interpolation between assessment points. Cost data are collected at the same assessment time points using a purpose-built cost questionnaire covering direct medical costs, direct non-medical costs, and indirect costs attributable to productivity loss. In-trial intervention costs are calculated by multiplying the recorded number of sessions by the corresponding prespecified unit costs. After unblinding, researchers obtain costs incurred at the study sites from the participating sites’ billing and electronic records. All resource-use costs will be valued in 2026 Korean won. Where cost inputs originate from earlier calendar years, they will be converted to the 2026 price year using the Korean Consumer Price Index. Because the analytic time horizon is 12 weeks and therefore less than 1 year, neither costs nor health outcomes will be discounted. The economic evaluation will follow the relevant recommendations of the Korean pharmacoeconomic evaluation guideline [25] and the CHEERS 2022 reporting standards [26]. Productivity loss is valued using the human-capital approach because the cost questionnaire does not collect the return-to-work timing data required to apply the friction-cost method.

### Safety monitoring

All adverse events (AEs), regardless of their relationship to the intervention, are recorded and classified according to severity as mild, moderate, or severe. Causality is rated as definitely related, probably related, possibly related, probably not related, not related, or unknown. Anticipated device-related AEs are expected to be mild and transient and may include eyestrain, dizziness, and mild physical discomfort associated with routine head-mounted display use. No independent Data and Safety Monitoring Board (DSMB) was established because the trial was considered to pose minimal risk. The underlying ETE therapeutic content is already used in routine Korean medicine practice, and the additional technological component consists of a brief, non-invasive head-mounted display-based training segment. All serious adverse events (SAEs) are reported by the investigator to the principal investigator and the IRB within 24 hours, regardless of causality. The principal investigator may suspend part or all of the trial pending further review or instruction from the IRB. No interim efficacy analysis or formal statistical stopping rule is prespecified. Safety oversight is based on continuous AE monitoring, expedited SAE reporting, and review by the principal investigator and the IRB.

### Statistical analysis

Clinical and economic analyses will be conducted using R software (version 4.3.2; R Foundation for Statistical Computing, Vienna, Austria) and StataMP version 16 (StataCorp LLC, College Station, TX, USA). QEEG and HRV indices will be extracted using NeuroGuide version 3.4.0 and the SA-3000P software, respectively. The exact software and package versions used will be reported after completion of the final analysis.

#### Analysis populations.

The primary efficacy analysis will follow the ITT principle and include all randomized participants according to their originally assigned treatment group, regardless of treatment adherence, withdrawal from treatment, protocol deviations, or the study site at which they were enrolled. Accordingly, all participants randomized at Wonkwang University Sanbon Hospital before recruitment at that site ended will remain in the ITT analysis and will not be excluded because of the site closure. Any imbalance between sites will be accounted for by including study site as a covariate in the prespecified efficacy models. Missing week-8 outcome data will be addressed using multiple imputation. A PP population will be used for sensitivity analyses and will exclude participants who complete less than 75% of the prescribed intervention sessions or who have major protocol deviations considered likely to affect efficacy assessment. Baseline demographic and clinical characteristics, including age, sex, study site, baseline PCL-5-K score, and the index trauma type recorded during the SCID-5 interview, will be summarized descriptively by treatment group. No significance testing of baseline balance will be performed; any imbalance will be described and considered in the interpretation of the results.

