#### Participant withdrawal criteria.

Participants are withdrawn for (1) non-compliance with investigator instructions, (2) protocol violations, (3) occurrence of serious adverse events, or (4) withdrawal of consent or a request to discontinue. Adherence is defined as (number of sessions actually completed ÷ number of sessions scheduled) × 100, recorded at every treatment visit. Participants with adherence below 75% will be excluded from the per-protocol (PP) analysis but will remain in the intention-to-treat (ITT) analysis. Participants who discontinue the assigned intervention but do not withdraw consent for follow-up will be encouraged to complete all scheduled outcome assessments whenever possible.

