#### Control group.

The waitlist control group receives no ETE intervention during the 8-week randomized intervention period but receives telephone check-ins every 2 weeks. Waitlist participants complete the week-12 follow-up assessment at the same time as participants in the active intervention groups. No booster or maintenance intervention is provided to any group between weeks 8 and 12; this interval is used solely for follow-up monitoring and assessment. No waitlist participant will begin ETE or VR-based ETE before the week-12 follow-up assessment has been fully completed. Only after completion of this final randomized-phase assessment may waitlist participants elect to receive 8 weeks of VR-based ETE, comprising 16 sessions, free of charge. The per-visit transportation stipend provided during the randomized phase is not provided for this post-trial intervention.

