#### Economic analysis.

The primary economic outcome will be the incremental cost per QALY gained. QALYs will be calculated from EQ-5D utility scores using the area-under-the-curve method, with linear interpolation between assessment points. The secondary economic outcome will be the incremental cost per unit improvement in EQ-VAS score. The two primary economic comparisons will mirror the confirmatory clinical comparisons: VR-based ETE versus the waitlist control condition and standard ETE versus the waitlist control condition. The comparison between VR-based ETE and standard ETE will be reported as an exploratory secondary economic comparison. The base-case within-trial economic evaluation will cover the 8-week intervention period and the subsequent assessment-only follow-up through week 12. Costs and health outcomes will be analyzed using the same ITT population as the primary clinical analysis. The PP population will be examined in sensitivity analyses. For each comparison, mean costs, mean QALYs, incremental costs, incremental QALYs, and incremental cost-effectiveness ratios will be estimated. Sampling uncertainty surrounding costs, QALYs, and incremental cost-effectiveness ratios will be examined using nonparametric bootstrapping. Cost-effectiveness planes and cost-effectiveness acceptability curves will be presented where appropriate. Because the 12-week horizon is insufficient to represent the long-term course of PTSD, the analysis is not intended to establish long-term or lifetime cost-effectiveness. Rather, it will generate preliminary short-term estimates of costs, utilities, QALYs, and uncertainty that may serve as candidate input parameters for future decision-analytic modeling, including a longer-term Markov model if appropriate external transition and recurrence data become available.

Missing cost, EQ-5D-5L, and EQ-VAS data in the within-trial analysis will be addressed using multiple imputation under a missing-at-random assumption. Because cost data are commonly right-skewed, appropriate generalized linear models or bootstrap-based methods will be used when estimating between-group differences in mean costs.

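### The 75% session rule can remove people only from the two therapy arms, so the per-protocol contrasts against waitlist are not randomized comparisons

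*Protocol article*

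**What the plan says.** Two places in the protocol article set the rule. Participant withdrawal criteria gives the measure, "Adherence is defined as (number of sessions actually completed ÷ number of sessions scheduled) × 100", and the consequence: "Participants with adherence below 75% will be excluded from the per-protocol (PP) analysis but will remain in the intention-to-treat (ITT) analysis". Analysis populations says that the PP set "will exclude participants who complete less than 75% of the prescribed intervention sessions", and adds a second ground for exclusion: "or who have major protocol deviations considered likely to affect efficacy assessment".

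Under Interventions, the two therapy groups "receive 16 treatment sessions over 8 weeks". The waitlist group gets telephone check-ins and assessment visits but no sessions, and Control group states: "No waitlist participant will begin ETE or VR-based ETE before the week-12 follow-up assessment has been fully completed".

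The PP set is used twice. Under Missing data: "The PP analysis will provide an additional supportive sensitivity analysis". Under Economic analysis: "The PP population will be examined in sensitivity analyses". Both Dunnett-adjusted clinical contrasts and both primary economic comparisons are against waitlist.

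**The concern.** An adherence threshold that exists in only one of the arms compared undoes the randomization for that comparison. Low attenders leave the therapy arms. The waitlist participants who would have attended poorly cannot be identified, and they stay. Any PP difference then mixes a treatment effect with a difference in who is left.

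At stake is how the sensitivity analyses are read. If PP agrees with ITT, a report will tend to present that as support for the result against waitlist. The agreement is weak support if the PP contrast carries a selection bias of unknown size. Nor does the PP contrast estimate the effect of receiving the intended number of sessions. The article does not mention the asymmetry, and it is not among the eight limitations in the Discussion.

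**Working it through.** **Where the rule applies**
- Therapy arms: 0.75 × 16 = 12. A participant with 12 sessions (75%) stays; one with 11 (11/16 = 68.75%) leaves.
- Waitlist: 0 sessions completed out of 0 scheduled, which is undefined. Counting it as below 75% would remove the whole arm, which cannot be meant. No parallel rule, such as calls answered or visits attended, is stated.
- VR-ETE versus ETE: the rule applies in both arms.

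**The plan's own figure.** The stated sample size is not in dispute. For ANCOVA with f = 0.5, alpha 0.05, three groups and one covariate, noncentrality f²N and N − 4 denominator degrees of freedom, the smallest N with 95% power is 65 (power 0.9502). At 72 the power is 0.9685.

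**Size of the bias, with no true treatment effect.** Let q be the share of a therapy arm excluded, and g the amount by which the excluded would have scored worse than the retained, in SD of PCL-5-K. The retained mean is the arm mean minus q × g, so the PP contrast shifts by −q × g (negative means lower PCL-5-K under therapy). The documents give neither q nor g; the ranges below are assumptions.

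| q | g (SD) | −q × g | Simulated PP |
|---|---|---|---|
| 10% | 0.3 | −0.03 | −0.036 |
| 20% | 0.5 | −0.10 | −0.106 |
| 30% | 0.8 | −0.24 | −0.241 |

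(Simulation: 24 per arm, baseline correlation 0.5, 3,000 runs per cell. The ITT estimate stayed within about 0.01 SD of zero.)

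**Second parameterization.** Let ρ be the correlation between latent adherence and a better outcome. The shift is −ρ × φ(z_q)/(1 − q) residual SD.

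| q | ρ = 0.3 | ρ = 0.5 | ρ = 0 | ρ = −0.3 |
|---|---|---|---|---|
| 10% | −0.058 | −0.097 | 0 | +0.058 |
| 20% | −0.105 | −0.175 | 0 | +0.105 |
| 30% | −0.149 | −0.248 | 0 | +0.149 |

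With exclusion in both therapy arms and ρ of 0.3 or 0.5, the simulated type I error of the PP omnibus test was 5.3% to 12.3% against a nominal 5% (4,000 runs per cell). At ρ = 0 it was 4.4% to 5.0%.

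**Scale**
- With 24 per arm, the standard error of a pairwise difference is √(2/24) = 0.29 residual SD. With baseline correlation 0.5 this is 0.29 × √0.75 = 0.25 outcome SD. A shift of 0.10 SD is 0.10/0.25 = 0.4 standard errors.
- If the two therapies are equally effective, f = d√2/3, so f = 0.5 implies d = 1.06. A shift of 0.10 SD is about a tenth of that.

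**What an instrumental-variable estimate would give.** With waitlist exposure zero and p the mean fraction of the 16 sessions received in the therapy arm, the estimate is (ITT difference)/p.
- Clinical: if p were 0.8 (illustrative), the estimate is 1.25 times the ITT difference, with a correspondingly wider interval. In a simulation with assumed attendance, its t-ratio correlated 0.999 with the ITT t-ratio, and the two agreed on significance in 98% of runs.
- Economic: (ΔCost/p)/(ΔQALY/p) = ΔCost/ΔQALY. The ratio is the ITT ratio again.

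**The case against.** **PP is supportive only.** This stands. The primary analysis is ITT with multiple imputation, the base-case economic analysis uses the same population, and PP sits beside a mixed model on all available data and, where appropriate, a complete-case analysis. No confirmatory decision rests on it. A reader might infer that the primary result is compromised; the documents do not support that.

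**The direction is assumed.** This stands. A reader might infer that PP favours therapy by construction. Only the asymmetry is built in. The article gives no attendance or prognosis data, and the bias would reverse if early responders stopped attending. For the cost-effectiveness ratio the direction is less certain still: dropping low attenders also raises mean session cost, because intervention cost is sessions times unit cost.

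**The waitlist is not wholly unselected.** This stands too. The major-deviation clause can remove people from any arm, so the asymmetry concerns attendance only.

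**The denominator.** One section speaks of scheduled sessions and the other of prescribed ones. A reader might infer that someone who leaves after attending 6 of 6 booked sessions counts as 100% adherent rather than 6/16 = 37.5%. No section says that only sessions booked so far are counted, and with 16 sessions fixed both words naturally mean 16. Aligning them is tidying.

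**The remedy is not a fragility check.** This stands. The instrumental-variable test nearly repeats the ITT test. It also requires that allocation acts only through sessions, which is open to doubt when participants are unblinded and report the outcome themselves.

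**The detail may be in the full protocol or an SAP.** PP membership for waitlist participants could be worked out there. But the article itself fixes the rule, the threshold and the uses of the PP set, and as fixed they give a one-sided exclusion in the contrasts that matter most.

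**Conclusion.** The point holds as a matter of design. Applied as written, the session rule selects on attendance in the therapy arms and cannot do so in the waitlist arm, so the PP contrasts against waitlist are not randomized comparisons. That conclusion needs no assumption about direction.

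The size does. If low attenders would have done worse untreated, PP leans toward benefit by roughly 0.03 to 0.25 SD over the ranges tried, and by about 0.10 SD at 20% excluded with a 0.5 SD gap. That runs from small to most of one standard error of a pairwise contrast. The consequence is limited to what the PP results may be used to claim.

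**What to change.** - **Clinical PCL-5-K contrasts against waitlist.** As the adherence analysis, replace the session-based PP analysis with a complier-average (instrumental-variable) estimate: randomized arm as instrument, sessions completed out of 16 as exposure (0 in waitlist), and the same baseline and site covariates. State that it assumes allocation acts only through sessions and that the effect is linear in dose. State also that its interval is wider and that its test largely repeats the ITT test. Present it as an estimate of the effect of sessions received.
- **Any 75% PP set still reported against waitlist, clinical or economic.** Label it non-randomized, and do not cite its agreement with ITT as evidence of robustness.
- **Cost-effectiveness ratio.** Do not use the instrumental-variable estimate here, since it returns the ITT ratio.
- **VR-ETE versus ETE.** Keep the 75% rule for this exploratory comparison, with the caveat that VR may change who attends, so this contrast can be selected too.
- **Denominator.** Use the 16 prescribed sessions in both Participant withdrawal criteria and Analysis populations.

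The cost is analysis wording. Session counts are already recorded and recruitment is still open, so the change can be specified before analysis.
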